**Interaction with tau and amyloid pathology (MCI/AD continuum).**
*Hypothesis 6:* In MCI, higher cortical hyperexcitability is associated with distinct CSF and plasma levels of tau and amyloid-β (Aβ40, Aβ42, t-tau, p-tau181) and with an unfavorable Aβ42/Aβ40 ratio.
**Impact on memory maintenance and consolidation.**
*Hypothesis 7:* Hyperexcitability is associated with impaired short-term retention and overnight consolidation of verbal memory.
**Impact on sleep architecture and spindle dynamics.**
*Hypothesis 8:* Hyperexcitability is associated with disrupted sleep architecture, altered N2/N3 power spectra, and reduced or disorganized slow and fast sleep spindles, which in turn mediate effects on memory consolidation.

## Methods

2

### Study design

2.1

This is a prospective, single-center, multimodal observational study being conducted at the Nyírö Gyula National Institute of Psychiatry and Addictology, led by the Neurocognitive Research Centre (NRC) in Budapest, Hungary. The study began in 2023 and is expected to terminate in 2028. The project comprises a cross-sectional, multimodal phenotyping of four groups (MCI, ASD, ADHD, and healthy controls; *N* = 75 per group) with standardized neuropsychological testing, structural MRI, resting-state fMRI, 24-h ambulatory EEG, and blood/CSF biomarkers. We are also performing a nested mechanistic substudy in a subset of participants across all groups who exhibit markers of cortical hyperexcitability. These participants are undergoing a 3-day in-ward protocol with continuous video-EEG, repeated neuropsychological testing, sleep staging and spindle analysis, and serial blood sampling. The study duration is 5 years, with the first 3 years focused on recruitment and baseline assessments, and the subsequent years emphasizing mechanistic analyses and dissemination. The protocol is summarized in Figure 1.

**FIGURE 1 F1:**
[figure not shown]
Overview of the LENDÜLET Neurocognitive Research Project design and workflow. MCI, mild cognitive impairment; ADHD, attention deficit/ hyperactivity disorder; ASD, autism spectrum disorder; HC, healthy control; DSM, Diagnostic and Statistical Manual of Mental Disorders, 5th Edition; EEG, electroencephalography; MRI, magnetic resonance imaging; rs, resting-state; fMRI, functional magnetic resonance imaging; CSF, cerebrospinal fluid; BBM, blood-based biomarkers; Aβ, amyloid-beta.

The proposed design is a pooled cross-diagnostic study protocol involving three patient populations and integrating data across these groups to identify shared and distinct neurobiological mechanisms. This study design has drawn increasing attention in the literature on neuropsychiatric disorders (Kan et al., 2023; Wigman et al., 2015). We are recruiting participants based on established diagnostic criteria, alongside age- and sex-matched healthy controls. Clinical, cognitive, and neuroimaging data will be harmonized across cohorts, ensuring comparable measures of executive function, memory, and social cognition. Structural and functional MRI, as well as EEG, are assessing neural network connectivity, focusing on regions implicated in excitation/inhibition (E/I) balance, such as the prefrontal cortex, hippocampus, and sensory cortices. We are using additional assays, including plasma and cerebrospinal fluid biomarkers, capturing molecular signatures of synaptic regulation and inhibitory neurotransmission. This approach enables identification of transdiagnostic neural signatures that transcend categorical diagnoses, offering a framework for understanding common circuit dysfunctions underlying both neurodevelopmental and neurodegenerative conditions.

### Participants

2.2

#### Eligibility criteria

2.2.1

Four groups are in recruitment:

MCI (older adults at risk for AD):Age: ≥ 55 yearsMeeting Petersen’s criteria for MCI: subjective cognitive complaint corroborated by an informant, objective impairment in at least one cognitive domain, preserved basic activities of daily living, absence of dementia (Petersen, 2016).Supporting evidence from structural MRI and neuropsychology.

ASD:Adult participants fulfilling DSM-5 criteria for ASD, based on standardized clinical assessment and validated instruments (Murphy et al., 2016).

ADHD:Adult participants fulfilling DSM-5 criteria for ADHD, based on structured clinical assessment and established rating scales (Young and Goodman, 2016).

Healthy controls (HC):No subjective cognitive complaints.Normal neurological examination and neuropsychological performance.Normal structural MRI and routine laboratory tests.No history of major psychiatric or neurological disease.

#### General exclusion criteria

2.2.2

Applied across all groups to reduce confounders:

History of central nervous system infection, significant brain lesions (stroke, extensive small-vessel disease, white matter infarcts), demyelinating disease, hydrocephalus, or major head trauma with loss of consciousness.Untreated vitamin B12 deficiency, hypothyroidism, syphilis, or HIV infection.Major depressive episode, schizophrenia, intellectual disability, or current substance dependence.Renal or hepatic failure, or other serious systemic illness likely to affect cognition.Current use of psychoactive medications significantly affects EEG/fMRI/neuropsychology (e.g., high-dose benzodiazepines, barbiturates), unless the dose is stable and deemed acceptable by investigators.Established epilepsy or history of unprovoked seizuresStandard contraindications to MRI (e.g., ferromagnetic implants, pacemaker, unstable cardiac disease).

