#### Resting-state fMRI

2.3.3

Resting-state fMRI will be acquired using T2*-weighted echo-planar imaging (EPI) sequences (TR 2,000 ms; TE 30 ms; flip angle 70–79°; voxel 3 × 3 × 3–4 mm; ∼10-min duration). Participants will be instructed to remain still, keep their eyes closed (or fixate on a cross, as per the scanner-specific protocol), and avoid falling asleep.

Preprocessing and functional connectivity analysis will be performed with the CONN toolbox (MATLAB) using a standard pipeline:

Realignment and unwarping; slice-timing correction.Outlier detection (ART-based scrubbing).Direct segmentation and normalization (GM/WM/CSF, MNI space).Spatial smoothing.Band-pass filtering (0.008–0.09 Hz).Regression of white matter, CSF, and motion parameters.

Regions of interest (ROIs) will be defined *a priori* within the DMN, SN, and AN based on the literature and group consensus. Seed-based connectivity (SBC) analyses will compute Fisher-z-transformed correlations between ROI time series and voxel-wise signals. Age and sex will be included as covariates. Group differences (e.g., HC > MCI, HC > ASD, HC > ADHD) will be evaluated using voxel-wise ANCOVA with cluster-level FDR correction (cluster pFDR < 0.05; voxel *p* < 0.001 uncorrected). Hyperactivity will be defined as significantly elevated connectivity or activity within predefined network ROIs of DMN, SN, and AN relative to HC normative values obtained from our reference database (ACOL). For further details, see section “2.4.1 Participant selection and extraction of normative values.” Participants will be categorized as fMRI-positive or fMRI-negative for cortical hyperexcitability. The exact fMRI pipeline is characterized in previous studies published by our group (Bolla et al., 2023, 2025).

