#### Cross-sectional analyses

2.6.1

Data from all diagnostic groups will be pooled into a single multivariate dataset and analyzed using machine learning and dimensional reduction techniques to extract cross-diagnostic patterns of neural and behavioral variance. The model will test for latent factors reflecting shared E/I imbalance across disorders, while *post hoc* analyses identify disorder-specific deviations. Statistical adjustments will account for confounders such as age, medication, and cognitive status.

Primary outcome will be the (Torenvliet et al., 2023) incidence and distribution of SEA, and fMRI hyperactivity in each diagnostic group relative to controls. Secondary outcomes will include relationships between hyperexcitability and (a) structural atrophy and white matter integrity; (b) functional connectivity within and between default mode, salience, and attention networks; (c) CSF and plasma tau/Aβ levels; and (d) domain-specific cognitive performance.

Incidence of hyperexcitability (primary outcome):○Logistic regression models comparing SEA and fMRI-positive status between groups (MCI, ASD, ADHD vs HC), adjusting for age, sex, education, and disease duration where applicable.○Results will be reported as odds ratios with 95% confidence intervals.

Associations with cognition, structure, and connectivity (secondary outcomes):○Within each group, participants will be classified as hyperexcitability-positive vs negative (see section “2.4.1 Participant selection and extraction of normative values”).○For continuous outcomes (neuropsychological scores, cortical thickness/volume, DTI measures, functional connectivity indices, blood-based biomarker concentrations), group comparisons will use *t*-tests or Mann–Whitney U tests depending on normality (Shapiro-Wilk).○For categorical variables, chi-square tests will be used.○Multivariable linear models with covariates (age, sex, education, disease duration, mood/anxiety scores) will assess independent associations.Holm–Bonferroni corrections will be used to control for multiple comparisons.

Cross-modal relationships:○Correlation and regression analyses will examine relationships between spike density and fMRI hyperactivity.○Multimodal latent variable models or clustering approaches will be applied exploratorily to define hyperexcitability phenotypes.

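### Stable-dose psychoactive drug users are eligible, but the primary and secondary covariate lists omit the medication adjustment that the same section promises

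*Protocol article*

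**What the plan says.** **Eligibility.** Section 2.2.2 excludes current psychoactive medication with a significant effect on EEG, fMRI or neuropsychology, "unless the dose is stable and deemed acceptable by investigators". The rule and its exception are headed "Applied across all groups to reduce confounders", so controls fall under them too. Section 2.2.1 requires of healthy controls "No history of major psychiatric or neurological disease". It does not require them to be drug-free.

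**Analysis.** The opening paragraph of Section 2.6.1, which describes the pooled machine-learning analysis, ends: "Statistical adjustments will account for confounders such as age, medication, and cognitive status". Further down, the primary logistic models for SEA and fMRI-positive status are specified as "adjusting for age, sex, education, and disease duration where applicable". For the secondary outcomes the section states: "Multivariable linear models with covariates (age, sex, education, disease duration, mood/anxiety scores) will assess independent associations". For the fMRI group contrasts, Section 2.3.3 says "Age and sex will be included as covariates".

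**The concern.** The main study is cross-sectional. A stable dose protects a before-after comparison in the same person, because the drug effect is the same at both times. It does not protect a comparison between people measured once: a drug that changes spike counts, connectivity or test scores does so on the day of measurement, however long the dose has been steady.

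If drug use differs between groups, the primary odds ratios carry part of that difference. Controls are probably less often medicated, because they have no major psychiatric or neurological history while patients come largely from dementia, ASD and ADHD clinics (Section 2.2.3). That is an inference; the article gives no drug-use figures. The same problem reaches Hypotheses 2 to 4, where hyperexcitability-positive and -negative people within a group are compared on cognition, structure and connectivity: a drug that affects both the label and the outcome confounds the association.

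Section 3.2 would read higher positivity in patients than in controls as support for a transdiagnostic phenotype. Medication is not among the limitations in Section 3.5.

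**Working it through.** The plan states no figure on this point, so there is none to reproduce. The check sets the lists side by side, then illustrates the possible size.

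**1. Where medication is named**

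| Place | Listed adjustment | Medication? |
|---|---|---|
| 2.6.1, pooled analysis paragraph | age, medication, cognitive status (as examples) | yes |
| 2.6.1, primary logistic models | age, sex, education, disease duration | no |
| 2.6.1, secondary linear models | the same plus mood/anxiety scores | no |
| 2.3.3, voxel-wise fMRI contrasts | age, sex | no |
| 2.4.1, fMRI normative values | age, sex, head motion (as examples) | no |
| 2.4.1, EEG spike-density threshold | age, sex, sleep state, montage | no |

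Neither the positive/negative label nor the models that use it name medication. The article does not say whether the sentence in the pooled-analysis paragraph also governs the other models.

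**2. Illustration with no disease effect**

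Assumptions: 5% positive off drug (in line with the 95th-percentile EEG threshold in Section 2.4.1); 2% of controls medicated; drug use in patients and the drug odds ratio varied. Drug use and drug effect are not in the documents.

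Positivity on drug: p_d = o/(1+o), with o = OR_drug × 0.05/0.95. Group positivity: m × p_d + (1−m) × 0.05, where m is the share medicated.

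Example, OR_drug = 2 and 40% of patients medicated: o = 0.1053, p_d = 0.0952. Controls: 0.02 × 0.0952 + 0.98 × 0.05 = 0.0509. Patients: 0.40 × 0.0952 + 0.60 × 0.05 = 0.0681. Apparent OR = (0.0681/0.9319)/(0.0509/0.9491) = 1.36.

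| Drug OR | 20% of patients medicated | 40% | 60% | 80% |
|---|---|---|---|---|
| 0.5 | 0.91 | 0.81 | 0.70 | 0.60 |
| 1.5 | 1.09 | 1.19 | 1.28 | 1.38 |
| 2 | 1.17 | 1.36 | 1.56 | 1.76 |
| 3 | 1.32 | 1.69 | 2.08 | 2.48 |

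**3. Illustration of masking**

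Assume 5% positive in controls and 15% in untreated patients (the prevalence assumed in Section 2.2.4): OR = (0.15/0.85)/(0.05/0.95) = 3.35. If a share f of patients takes a drug that multiplies positivity by r, patient positivity is 0.15 × (1 − f + f × r). With f = 0.2 and r = 0.5 this is 0.135, OR 2.97. With f = 0.6 and r = 0.25 it is 0.0825, OR 1.71.

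**4. What a medication term would do**

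Take one patient group against controls, with no treated controls. The model logit(p) = a + b × diagnosis + c × medication has three parameters and three occupied cells. Then a is the logit for controls and a + b the logit for untreated patients, so exp(b) is exactly the odds ratio of untreated patients against controls. A medication term and a restriction to unmedicated people therefore target nearly the same contrast; further covariates or a few treated controls change this only a little.

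**5. Precision of the unmedicated contrast**

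For 5% against 15% positive, two-sided 0.05 and 75 controls, power = Φ[(0.10 − 1.96 × SE0)/SE1], where SE0 uses the pooled proportion and SE1 the separate ones. With 75 unmedicated patients SE0 = 0.0490 and SE1 = 0.0483, giving 53%. With 60, 45, 30 and 15 unmedicated patients (20%, 40%, 60%, 80% medicated) power is 51%, 47%, 42% and 34%.

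**The case against.** **Medication is not ignored.** Section 2.6.1 names it, and drug coding and sensitivity analyses are usually left to an analysis plan that is not shown. The second part is fair as to detail. But the article prints explicit covariate lists that differ from its own sentence on confounders; that is stated text to reconcile, not an omission.

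**Exclusion is the default.** The exception needs both a stable dose and investigator acceptance, and Section 2.2.2 also excludes epilepsy, unprovoked seizures, major depressive episode, schizophrenia and substance dependence, which removes main indications for anti-seizure and antipsychotic drugs. This stands. It limits drug use to an unknown extent but does not remove it.

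**Stronger readings that the documents do not support.**
- A reader might infer that only patients may enter on drugs. The exception covers all groups.
- A reader might infer that drug effects will be reported as disease effects. Drug use, drug effect and direction are all unknown, and Section 3.5 disclaims definitive causal inference.
- A reader might think that a medication term cannot help because few controls are treated. Step 4 of the working shows otherwise. The real weakness is that treated and untreated patients may differ in severity, and restriction shares that weakness.
- A reader might extend the point to Hypotheses 7 and 8. These rest largely on within-subject models with random intercepts (Section 2.6.2), where a stable dose does help.

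**Conclusion.** The point holds as an internal inconsistency with consequences for the primary analysis. The protocol identifies psychoactive drugs as affecting its outcome modalities, admits some users, promises adjustment for medication, and then lists primary and secondary models without it. Run as listed, those models leave an acknowledged confounder uncontrolled in the patient-versus-control odds ratios and in the between-person tests of Hypotheses 2 to 4.

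The size is not known. On the assumptions shown, a null could appear as an odds ratio anywhere from 0.60 to 2.48, and a true 3.35 could shrink to between 2.97 and 1.71. These figures show only that bias in either direction is possible; they are not estimates for this study. That controls are less often medicated is likely from their selection criteria but is not stated.

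**What to change.** Eligibility need not change.

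1. In Section 2.6.1, reconcile the general sentence with the lists: say which models carry medication, and add medication use, by drug class where numbers allow, to the within-group secondary linear models.
2. For each primary contrast, pre-specify alongside the main model a sensitivity analysis in participants taking no psychoactive or anti-seizure drug at the EEG and MRI, or the nearly equivalent model with a medication term. Interpret it by estimate and confidence interval. It should not be a pass/fail rule for attributing a difference to the disorder: at the power shown, chance alone could overturn a true effect.
3. Add residual confounding by medication to the limitations in Section 3.5.

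**Cost.** This is analysis wording. Study data are stored in ACOL (Section 2.3), whose records include medications (Section 2.4.1). Because assessments may spread over three months, check that drug use is recorded as of each EEG and MRI. Intervals in the unmedicated set will be wider, and unmedicated patients may be milder cases, so agreement with the main model supports the finding without proving that drugs play no part.

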#### Recruitment and consent

2.2.3

We are recruiting from:

Outpatient clinics of the National Hospital for dementia/MCI, ASD, and ADHD.In-house patient registries, including the AlzEpi Cohort Observational Library (ACOL).Collaborating with outpatient neurology and psychiatry services.Patient organizations and community outreach.

Potentially eligible individuals are receiving written and verbal information about the study. Written informed consent will be obtained from all participants (or legally authorized representatives if required) prior to any study-specific procedures. The entire study, including recruitment, data acquisition, data analysis, and reporting, will be carried out by the same team (neurologist, neuropsychologist, neurophysiologist, MRI assistant, radiologists, and clinical researchers) throughout.

#### Sample size justification

2.2.4

Power calculations for the primary cross-sectional study were informed by previous investigations of cortical hyperexcitability and subclinical epileptiform activity (SEA) in neurocognitive disorders [summarized by Horvath et al. (2020)]. Assuming a medium effect size (Cohen’s *d* = 0.5), a two-sided significance level of α = 0.05, and four diagnostic groups, a sample size of 75 participants per group (total *N* = 300) provides more than 90% power to detect clinically meaningful between-group differences in the primary outcomes, including the incidence of SEA and resting-state fMRI hyperactivity.

The mechanistic in-ward substudy is enrichment-based and will include participants demonstrating evidence of cortical hyperexcitability. Assuming a conservative prevalence of approximately 15% across the clinical groups, we anticipate recruiting approximately 45 eligible participants, with an expected final sample of approximately 40 after accounting for an estimated 20% attrition rate.

The mechanistic substudy is designed primarily to characterize within-subject physiological relationships among cortical hyperexcitability, sleep architecture, memory consolidation, and circulating biomarkers using repeated-measures analyses. Because repeated observations substantially increase statistical efficiency for within-subject comparisons, this sample size is considered appropriate for estimating effect sizes, assessing feasibility, and identifying candidate mechanistic pathways. In contrast, more analytically demanding models, including formal mediation analyses and subgroup comparisons across diagnostic categories, are expected to have limited statistical power with the anticipated sample size. Accordingly, these analyses will be considered exploratory and hypothesis-generating, with emphasis placed on effect size estimation, confidence intervals, and model uncertainty rather than statistical significance alone. Findings from these exploratory analyses will inform sample size calculations and analytic strategies for future confirmatory multicenter studies.

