To generate normative EEG values, we perform meticulous EEG preprocessing on 24-h recordings—artifact removal (e.g., eye blinks, muscle noise), filtering, and referencing—to ensure clean data. Two manual expert reviews of the files to identify potential SEA in line with the previously published protocols (Kamondi et al., 2024; Port et al., 2019). To define normal limits, the density, amplitude, duration, and spatial distribution of these events can be quantified across all control recordings. Statistically, normal values are represented by upper tolerance limits (the 95th percentile) of spike density (events per hour) computed from the control group. Normative modeling is applied to further refine these thresholds by accounting for age, sex, sleep state, and recording montage, variables known to influence EEG background and transient patterns. Additionally, spectral power and band ratios (delta, theta, alpha, beta, gamma) are used to construct normative baselines, against which epileptiform spikes produce transient deviations.

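### The claim of more than 90% power does not follow from its own inputs (86% per comparison with controls) and uses a mean-difference effect size for binary primary outcomes

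*Protocol article*

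**What the plan says.** Section 2.2.4 of the protocol article gives the inputs as "Assuming a medium effect size (Cohen’s *d* = 0.5"), "a two-sided significance level of α = 0.05, and four diagnostic groups", and "a sample size of 75 participants per group" (300 in total). It concludes that this "provides more than 90% power to detect clinically meaningful between-group differences in the primary outcomes, including the incidence of SEA and resting-state fMRI hyperactivity". It states no event rate for this calculation.

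Sections 2.3.3 and 2.3.4 label each participant positive or negative on fMRI and on EEG. Section 2.6.1 sets the primary analysis as "Logistic regression models comparing SEA and fMRI-positive status between groups (MCI, ASD, ADHD vs HC"), reported as odds ratios with 95% confidence intervals. After the secondary-outcome items it adds: "Holm–Bonferroni corrections will be used to control for multiple comparisons".

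Two other places bear on the rates. Section 2.4.1 says that for EEG "normal values are represented by upper tolerance limits (the 95th percentile) of spike density (events per hour) computed from the control group". For substudy recruitment, section 2.2.4 assumes a prevalence of about 15% in the clinical groups and calls it conservative.

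**The concern.** There are two separate faults. First, the stated effect size, alpha and group size can be put straight into a power formula, and the planned comparison with HC does not reach the stated figure. Second, Cohen's d describes a difference between two means in SD units, whereas the primary outcomes are proportions. Power for a comparison of proportions cannot be read from d; it needs the rate in controls and the rate in patients.

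Hypothesis 1, that hyperexcitability is more frequent in each patient group than in controls, rests on this calculation. If the assumed excess is modest and the control rate low, real power could be well below the stated level, and the article gives no means of seeing that.

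**Working it through.** **1. The stated inputs, planned pairwise contrast.** Inputs from section 2.2.4: d = 0.5, two-sided alpha 0.05, n = 75 per group. Contrast from section 2.6.1: each patient group vs HC.

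- Noncentrality = d × √(n/2) = 0.5 × √37.5 = 3.062.
- Normal approximation: Φ(3.062 − 1.960) = 86.5%.
- Exact noncentral t, 148 df: **86.0%**.
- Power is 89.99% at 85 per group and 90.3% at 86, so 90% needs **86 per group**.

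**2. Can the stated figure be recovered?** Four groups are listed among the inputs, so an omnibus ANOVA is a natural candidate (3 and 296 df, noncentrality λ = 300 × f²).

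- Hypothesis 1 pattern, means 0, 0.5, 0.5, 0.5 in SD units. The grand mean is 0.375, so f² = (0.375² + 3 × 0.125²)/4 = 0.0469, f = 0.217 and λ = 14.06. Power is **89.3%**.
- Conventional medium f = 0.25: λ = 18.75. Power is **96%**.

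The value f = 0.25 corresponds to d = 0.5 only if two groups sit at one extreme and two at the other, which is not the Hypothesis 1 pattern. A one-sided pairwise test gives 92% but contradicts the stated two-sided level. HC against all 225 patients pooled gives 96% but is not the planned contrast.

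**3. The binary primary outcome.** The test is approximated by the unadjusted pooled z-test of two proportions at 75 vs 75, with power by exact enumeration of both binomials. The rates are assumptions:

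- HC 5%: implied for SEA by the 95th-percentile limit; 10% is shown as an alternative.
- Patients 15%: the substudy figure.
- Patients 11.5%: d = 0.5 converted to an odds ratio, exp(0.5 × π/√3) = 2.48, and applied to 5%. The odds are 0.0526 × 2.48 = 0.130, so the rate is 0.130/1.130 = 11.5%.

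| HC | Patients | Power, alpha 0.05 |
|---|---|---|
| 5% | 11.5% | 31% |
| 5% | 15% | 55% |
| 5% | 20% | 83% |
| 5% | 25% | 95% |
| 3% | 20% | 94% |
| 10% | 20% | 41% |
| 10% | 30% | 88% |

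For 5% vs 15%, the normal approximation to the z-test gives 53% and Fisher's exact test 45%, so the choice of test does not change the picture.

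**4. Detectable difference at 90% power, 75 vs 75.** About 22% vs 5%, or about 31% vs 10%, at alpha 0.05. If Holm–Bonferroni covered all six primary contrasts (three patient groups × two markers), the first step would use 0.05/6, and 90% power would need about 27% vs 5%.

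**The case against.** The strongest reply is that the authors probably ran an omnibus four-group calculation with a medium f of 0.25, which does give 96%, and labelled it d. That is plausible and would make the fault partly one of labelling. It does not rescue the sentence: the stated measure is d, the planned tests are contrasts with HC, and the outcomes are still binary.

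The objections to the binary figures carry more weight. A reader might infer that the protocol itself supplies both rates and that true power is therefore about half the claim. The documents do not support that.

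- No HC rate is stated. The 5% is implied by a percentile limit that applies to SEA spike density only, is derived from the ACOL reference controls rather than this study's HC group, and is then refined for age, sex, sleep state and montage. No corresponding rate follows for fMRI.
- The 15% is a recruitment figure for participants positive on either marker, so a single marker may be rarer. It is also called conservative, so it may be higher. Its base is unclear: the 45 expected participants are 15% of 300 but 20% of the 225 patients (15% of 225 is about 34).
- Power above 90% is possible under other rates, such as 3% vs 20% or 5% vs 25%.

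A reader might also infer that alpha must be divided by six. The Holm–Bonferroni sentence follows the secondary analyses and is not said to govern the primary contrasts, so the adjusted figure is conditional. Nor does the article say that a non-significant group will be taken as showing no excess; the planned confidence intervals would display the imprecision.

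**Conclusion.** The power statement is wrong as written. Two parts of this need no assumption about rates: power is 86%, not more than 90%, for each planned two-sided comparison at the stated d, alpha and group size; and d does not describe the binary primary outcomes. The ANOVA reading that follows Hypothesis 1 also falls just short, at 89%.

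How far power falls for the actual primary test is conditional on the rates. With 5% in HC it runs from 31% to 95% as the patient rate goes from 11.5% to 25%, and it is about 55% at 15%. These figures ignore covariate adjustment, unusable recordings and multiplicity, each of which would tend to lower power. The supported conclusion is that more than 90% has not been shown and would require patient rates of roughly 22% or more against 5%. It is not that the study is known to have half its stated power.

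**What to change.** In section 2.2.4, delete the sentence claiming more than 90% power. Replace it with power, or the detectable difference, for the pairwise comparison of two proportions at 75 vs 75:

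- Give the assumed HC and patient rates separately for SEA and for fMRI positivity, as a range, with their basis.
- Report the detectable difference, for example about 22% vs 5% or about 31% vs 10% for 90% power at two-sided alpha 0.05.
- State the alpha used and whether Holm–Bonferroni covers the primary contrasts. If it covers all six, give the first-step figure of about 27% vs 5%.

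N = 300, the design and the analysis model stay as they are. The cost is a text change and a less favourable power statement; no extra participants are needed.

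### The in-ward substudy numbers do not agree: 45 recruited less 20% attrition is 36, not about 40, and 15% of the three clinical groups is about 34, not 45

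*Protocol article*

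**What the plan says.** The Sample size justification (section 2.2.4) sets "a sample size of 75 participants per group" for the main study. For the mechanistic substudy it gives a chain of three steps. The first two are a rate with its base and a recruited number: "Assuming a conservative prevalence of approximately 15% across the clinical groups, we anticipate recruiting approximately 45 eligible participants". The third is the number expected to complete: "with an expected final sample of approximately 40 after accounting for an estimated 20% attrition rate". It then judges that size adequate for estimating effects, assessing feasibility and finding candidate mechanisms, and it labels mediation and diagnostic-subgroup analyses exploratory.

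The Study design section (2.1) describes "cross-sectional, multimodal phenotyping of four groups (MCI, ASD, ADHD, and healthy controls" and, after Figure 1, "a pooled cross-diagnostic study protocol involving three patient populations". It opens the substudy to "a subset of participants across all groups who exhibit markers of cortical hyperexcitability". Section 2.4.1 confirms that positive healthy controls are invited as well as patients.

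**The concern.** Each number in the chain should follow from the one before it, and two steps do not. The recruited number does not follow from the stated rate and base, and the completing number does not follow from the recruited number and the stated attrition.

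At stake is the size on which the whole in-ward work package is judged adequate. The overnight memory, sleep and spindle questions (Hypotheses 7 and 8) draw on these participants, and the protocol intends the substudy's results to inform the sample sizes of later confirmatory studies.

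**Working it through.** **Inputs**
- Participants per group: 75 (section 2.2.4).
- Groups: 4 in all, of which 3 are patient groups (section 2.1). So 3 × 75 = 225 patients and 4 × 75 = 300 participants.
- Rate: 15%, attached to the clinical groups (section 2.2.4).
- Attrition: 20% (section 2.2.4).
- Stated results: about 45 recruited, about 40 final.

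**Formulas.** Recruited = rate × base. Final = recruited × (1 − attrition).

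**Step 1: reproduce the 45**
- Base as written: 0.15 × 225 = 33.75, about 34. Does not reproduce.
- All participants: 0.15 × 300 = 45. Reproduces exactly.
- To get 45 from 225, the rate would have to be 45/225 = 20%.

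**Step 2: reproduce the 40**
- From the stated 45: 45 × 0.80 = 36. Does not reproduce.
- Dividing by 1.2 instead: 45/1.2 = 37.5. Does not reproduce.
- From 33.75: 33.75 × 0.80 = 27. Does not reproduce.
- Attrition implied by 45 to 40: 1 − 40/45 = 11.1%.
- Recruitment needed for 40 at 20% attrition: 40/0.80 = 50, which is 22.2% of 225 or 16.7% of 300.

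**Step 3: could positive controls close the gap on the 225 base?** With a control rate r, final = (33.75 + 75r) × 0.80. Setting this to 40 gives r = (50 − 33.75)/75 = 21.7%. Controls would have to be positive more often than the 15% assumed for patients. At r = 15% the result is again 36.

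**Results**

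| Base for the 15% | Recruited | Final after 20% | Stated 40 is too high by |
|---|---|---|---|
| 300, pooled | 45 | 36 | 11% (40/36) |
| 225, as written, before any controls | 34 | 27 | 48% (40/27) |

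**Step 4: effect on precision.** For between-participant quantities the interval width scales as 1/√n. √(40/36) = 1.05 and √(40/27) = 1.22, so intervals are about 5% and 22% wider than at n = 40.

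**The case against.** The 45 has a sensible reading. Controls may enter the substudy, the preceding paragraph counts them among the four diagnostic groups, and 15% of 300 is exactly 45. The mention of clinical groups may simply be loose wording. This stands as far as it goes: the 45 may be a mislabelled base and not a miscalculation. It does not rescue the 40, which fails from 45 too.

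The 15% is called conservative, so the true yield may be higher. That is fair as a forecast, but the 45 and 40 are presented as following from 15% and 20%, and they do not. Nor does the word approximately cover the gap, since it would need attrition of about half the stated rate.

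The protocol claims no formal power for the substudy and already marks its most demanding analyses as exploratory. This stands and limits the severity.

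Some stronger readings are tempting, but the document does not support them:
- A reader might infer that 45 gives controls the patient rate and so contradicts Hypothesis 1. A pooled 15% need not. For illustration, controls at 5% (3.75 people) and patients at 18.3% (41.25 people) also add to 45.
- A reader might infer a control rate near 5% from the 95th-percentile limit in section 2.4.1. That limit covers EEG spike density only. The fMRI route also qualifies a participant, and its control rate is not given.
- A reader might infer that every positive participant is assumed to accept admission. The text does not say whether the 20% includes refusals.

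**Conclusion.** The point holds, at moderate severity. The final sample of about 40 does not follow from the stated inputs on either base. It is 36 if the 15% is a pooled rate over 300. It is 27 if the rate applies to the three clinical groups as written, plus whatever positive controls add. The step from 45 to 40 is the firmer error, because it does not depend on the base. The step from 15% to 45 is an error only if the stated base is taken literally.

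This rests on 75 per group being achieved and on the 15% and 20% being taken at face value. On the 225 base it also rests on controls not being positive at 21.7% or more, which would put them above the patients.

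One might conclude that the realistic yield is a quarter to a third smaller than planned. Only the literal 225 base with few positive controls gives that; on the pooled base the shortfall is 10% (36 against 40). The section also states no interval width or power for the substudy, so no numerical precision claim is overturned. What needs restating is the verbal judgement of adequacy. The primary cross-sectional analysis is unaffected.

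**What to change.** In section 2.2.4:
1. State the base for the 15%: either the 225 patients, with a separate stated rate for controls, or a rate pooled over all 300.
2. Make the recruited number, attrition and final number agree. On the 300 base this is 45 recruited and about 36 final. On the 225 base it is about 34 recruited and about 27 final, plus the expected controls. If 40 completers are wanted, state that 50 must be recruited and which rate would supply them.
3. While editing, say whether the 20% includes people who decline admission.
4. Rest the statement that the size is adequate on the corrected number.

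The cost is a few sentences of text. No procedure, endpoint or main-study sample size changes, but the stated substudy size becomes less favourable unless more participants are recruited.
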